## Abstract

**Background:**

Existing rehabilitation techniques are not satisfactory in improving motor function after stroke, resulting in heavy social burdens. With discovery of mirror neuron system (MNS), action observation (AO) has become a promising strategy to promote motor learning in rehabilitation. Based on MNS theory and virtual reality (VR) technology, we designed an innovative rehabilitative approach: synchronous 360° VR video AO (VRAO) and neuromuscular electrical stimulation (NMES). We hypothesized that VRAO+NMES could enhance MNS activation, thus to improve upper limb motor function and activities of daily living in stroke survivors.

**Methods:**

To explore the efficacy and mechanism of VRAO+NMES, we designed this single center, evaluator blinded, prospective, two arm parallel group randomized controlled trial with 1:1 allocation ratio. The experiment group will receive VRAO+NMES, while the control group will receive VR landscape observation combined with NMES. The Fugl-Meyer Assessment for Upper Extremity is the primary outcome of this study, Brunstrom Recovery Stages for Upper Extremity, Manual Muscle Test, Range of Motion, Modified Barthel Index, and Functional Independence Measure are the secondary outcomes. In addition, functional near-infrared spectroscopy (fNIRS) and surface electromyography (sEMG) will be used to evaluate the activation of MNS brain regions and related muscles, respectively.

**Discussion:**

Applying VR in AO therapy (AOT) has become popular, another study direction to improve AOT is to combine it with peripheral stimulations simultaneously. Due to its full immersive characteristic and multi-sensory input, 360° videos based VRAO+NMES could improve the motivation and engagement level of participants. In addition, fNIRS and sEMG test results may act as good biomarkers to predict rehabilitation outcomes, helping select suitable candidates for this new intervention.

**Conclusion:**

The results of this study will provide evidence for the feasibility and potential clinical efficacy of VRAO+NMES in stroke rehabilitation, thus to promote the clinical applicability and generalize its use in hospital, community, and home rehabilitation settings.

**Clinical trial registration:**

https://www.chictr.org.cn/showproj.html?proj=178276, Identifier [ChiCTR2200063552].

## Introduction

1

Stroke is the second-leading cause of mortality and the third-leading cause of disability globally (1). The physical, cognitive, and emotional disorders caused by stroke influence the patients’ life comprehensively and dramatically; approximately half of stroke survivors are chronically disabled and need long-term rehabilitation (2). Promoting changes in brain structural plasticity and functional reorganization are critical to rehabilitation of motor function following stroke (3). In physiotherapy, motor learning and relearning have become important strategies to induce neuroplasticity (4). Recently, the discovery of mirror neuron system (MNS) has further advanced our understandings of the neuroscientific mechanisms underlying motor learning and brain functional reorganization (5). Mirror neurons are a special class of neuron that excites during both observation and execution of actions. It is, therefore, possible to activate the motor system by simply observing actions without actual motor outputs (6).

The motor system has the potential to learn new skills or to recover from injury by observing others’ actions through activation of MNS (7). Meta analysis results have showed that AO therapy (AOT) is helpful to improve stroke patients’ upper extremity and hand functions, walking ability, and activities of daily living (ADLs); it has been accepted as an effective method in neurorehabilitation (8–10).

With technological advances, two important study directions have recently emerged to further promote motor learning effects induced by activation of MNS. The first direction is to change the implementation methods and techniques of AOT to improve participants’ engagement. The second direction is to combine AOT with other rehabilitation techniques, thus to obtain synergistic effects and improve treatment efficacy (11).

In the first research direction, virtual reality (VR) technology has become increasingly important. As a new modality of rehabilitative approach, VR can offer multisensory integration, including visual, tactile, vestibular, proprioceptive, interoceptive, emotional, and somatosensory inputs, creating a favorable rehabilitation environment (12). According to immersion level, VR can be divided into immersive, semi-immersive, and non-immersive VR (13). There are several types of immersive VR, graphical computational three-dimensional (3D) animations VR and 180°/360° videos VR are the most common ones (14). Compared with watching two-dimensional (2D) videos on a computer screen, participants can change their point of view freely to watch the demonstration from different angles wearing a VR headset (15).

With advances in technology, 360° videos based fully immersive VR treatments are becoming more accessible and flexible, playing an important role in enhancing wellbeing (16). The immersive feelings facilitate engagement and motivation of participants; 360° VR videos are good choices to improve immersive feelings (17). With the highest levels of immersion and reality, the novelty of 360° VR videos will make AOT more interesting and motivating. Furthermore, by capturing or displaying a full spherical view, 360° VR provides a more authentic and immersive experience, closely resembling real-life perception (18). As the result, the enhanced immersive feelings will motivate participants to view the videos and try to imitate the actions (19, 20). In addition, the high frame rate (e.g., 100 fps) of the modern 360° camera allows users to capture slow motions of the observed actions, helping to show step-by-step details of daily life actions.

The second research direction involves obtaining synergistic effects through combination of AOT with other rehabilitation techniques. This is mainly based on the theory that central-peripheral synchronous stimulations have the potential to improve brain activity (21). To further evoke plasticity in human motor system, AOT has been reported to be combined with different treatments, including transcranial magnetic stimulation (TMS), electrical stimulation (ES), and rehabilitation robots (11). The most common peripheral stimulation is low-frequency ES, which is a kind of physiotherapy modality used to improve motor and sensory function, including neuromuscular electrical stimulation (NMES), functional electrical stimulation (FES), and peripheral nerve stimulation (PNS) (22). When applying AOT+PNS in healthy individuals, the PNS-generated afferent signals from the periphery induce neural plasticity in primary motor cortex (M1) (23). Seitz et al. (24) studied the immediate effect of concurrent applications of AO, motor imagery (MI), and PNS, showing that AO+MI+PNS can induce plasticity in M1.

Based on the above background, we designed a new kind of rehabilitative technique: concurrent VR-based AO combine with NMES (VRAO+NMES). By playing immersive 360° videos in a VR headset, we present visual information to participants. We have tested the validity of combination of AO and NMES in a previous study, using 2D video clips of hand extension movements as the modality of AOT. We tested brain activation patterns of left MNS during AO, action execution, and imitation combined with NMES in healthy participants, the results proved that MNS-based rehabilitation approaches may enhance cortical activation of MNS (21). In addition, we also confirmed that compared with action execution and 2D video based action imitation, the activation of MNS was enhanced when combing them with NMES (11). Here, we will further test the VRAO+NMES application in stroke rehabilitation.

Due to the effects of action visual stimulation on MNS and ES on motor units (MUs), VRAO+NMES may be helpful to accelerate the process of motor learning. In addition, the enhanced multisensory interactions generated by VRAO+NMES have potential to improve the alteration of body ownership and induce self-body recognition (23). To investigate the potential neuromuscular control mechanism underlying this new intervention, we will use functional near-infrared spectroscopy (fNIRS) and surface electromyography (sEMG) to evaluate the activation of brain regions and muscles, respectively. In addition, MNS network-based neuroplasticity changes have been confirmed recently, we will also explore the brain functional connection changes before and after the interventions (25).

We, therefore, aim to determine whether a concurrent application of VRAO and NMES would result in significant improvements in behavioral assessments and neurophysiological parameters, and to test whether the changes in motor function evaluated by clinical scales are related to the brain functional imaging results measured by fNIRS. We hypothesize that VRAO+NMES is superior in improving upper extremity and hand motor functions, ADLs, and MNS cortical activation levels compared to conventional therapy plus NMES. The underlying mechanism may be that the brain-muscle synchronous intervention enhances activation of the MNS and recruitment of MUs, thereby promoting brain plasticity changes, improving neuromuscular control function, and enhancing therapeutic effects.

## Materials and methods

2

### Study design and settings

2.1

This study is a single center, evaluator blinded, prospective, two arm parallel group design randomized controlled trial (RCT) with a 1:1 allocation ratio (Figure 1). This trial protocol adheres to the Standard Protocol Items: Recommendations for Interventional Trial (SPIRIT) statement, and the SPIRIT 2013 checklist (26). The study results will be reported following the Consolidated Standards of Reporting Trials (CONSORT) statement and checked with the CONSORT 2010 checklist (27). The study will comply with the principles of Good Clinical Practice, and the Declaration of Helsinki and its amendments.

**Figure 1 fig1:**
[figure not shown]
Flowchart of study design according to CONSORT 2010. VR, virtual reality; AO, action observation; LO, landscape observation; NMES, neuromuscular electrical stimulation; FMA-UE, Fugl-Meyer Assessment for Upper Extremity; BRS-UE, Brunnstrom Recovery Stages for Upper Extremity; MMT, Manual Muscle Test; ROM, Range of Motion; MBI, Modified Barthel Index; FIM, Functional Independence Measure; fNIRS, functional near-infrared spectroscopy; sEMG, surface electromyography.

Each participant will voluntarily sign a written informed consent prior to inclusion. This study will be conducted at Beijing Bo’ai Hospital, China Rehabilitation Research Center (CRRC). This study was approved by the Medical Ethics Committee of CRRC (approval number: 2021-100-1). This study was registered in the China Clinical Trial Registration Center (Registration number: ChiCTR2200063552) and the Medical Research Registration Information System of the National Health Security Information Platform (Registration number: MR-11-23-018905).

### Participant timeline

2.2

The schedule of enrollment, allocation, interventions, and assessments of this study is following the SPIRIT statement (Figure 2). A follow-up survey will be conducted at 1 week after the end of the trial, including questionnaire surveys of safety, satisfaction, motivation, and feedback.

**Figure 2 fig2:**
[figure not shown]
Timeline of participant enrolment, allocation and analysis according to SIPIRIT 2013. VR, virtual reality; AO, action observation; LO, landscape observation; NMES, neuromuscular electrical stimulation; FMA-UE, Fugl-Meyer Assessment for Upper Extremity; BRS-UE, Brunnstrom Recovery Stages for Upper Extremity; MMT, Manual Muscle Test; ROM, Range of Motion; MBI, Modified Barthel Index; FIM, Functional Independence Measure; fNIRS, functional near-infrared spectroscopy; sEMG, surface electromyography; AEs, adverse events; SAEs, serious adverse events.

### Screening and recruitment

2.3

Patients with stroke will be recruited and screened for eligibility at Beijing Bo’ai Hospital. The study introduction poster and flyers will be distributed to potential participants. Detailed study information will be provided to all the intended participants and their caregivers by a trained researcher during the screening phase. Participants can contact the research coordinator to acquire more study information during their decision-making process. Recruitment stops once the pre-specified sample size is reached, or the preplanned interim analyses show the new intervention is unlikely to demonstrate benefit. All decisions will be reviewed by the Data Safety Monitoring Board and the Medical Ethics Committee.

### Participants

2.4

Patients with stroke will be recruited according to the following criteria.

#### Inclusion criteria

2.4.1

Participants will be included if they meet the following criteria: (1) Patients with a first-ever ischemic or hemorrhagic stroke, meeting the stroke diagnostic criteria established by the fourth National Conference on Cerebrovascular Disease of China in 1995, and confirmed by computerized tomography (CT) or magnetic resonance imaging (MRI); (2) Adults, aged 30–70 years old; (3) Within 6 months of stroke onset; (4) The disease is stable, neurological conditions and vital signs are no longer progressing; (5) The ability to sit independently for approximately 40 min to finish the treatments and assessments, including preparing time; (6) Without visual impairment, able to see the content of the experiment program; (7) Unilateral limb hemiplegia, Brunstrom Recovery Stages for Upper Extremity 3, 4, or 5 stage at the time of enrollment; (8) Right-handed, determined by the Edinburgh Handedness Inventory (EHI) – Short Form (28); (9) Chinese speaking; (10) Junior high school education or above; and (11) Willingness to provide informed consent and comply with the study protocol.

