#### Exclusion criteria

2.4.2

Participants will be excluded if they meet one of the following criteria: (1) With serious diseases, such as heart, lung, liver, and kidney failure; (2) With other neurological conditions that cause motor deficits, such as Parkinson’s disease, multiple sclerosis, and peripheral neuropathy; (3) Epileptic seizures; (4) With cognitive impairments, Mini-Mental State Examination (MMSE) ≤24 scores, unable to cooperate with researchers to finish the interventions or assessments; (5) With severe aphasia and communication difficulties that may influence the intervention and outcome measures; (6) With severe pain, Visual Analog Scale (VAS) ≥7 scores; (7) With moderate or severe depression, anxiety and other psychological disorders; (8) With contagious conditions or diseases, particularly of eyes, skin, scalp, or forearm; (9) With implanted medical devices or materials, such as pacemaker and metal implants; (10) With contraindications for NMES, such as skin injuries or skin diseases, acute infections, vascular diseases in the affected forearm; (11) With other diseases limiting upper extremity and hand functions, such as fracture, joint injury, and muscle pain of the affected arm; (12) With vestibular diseases, digestive problems that limit the use of VR headset; (13) Surgery and other invasive treatments; (14) Participants with a recurrent stroke or any medical condition that may affect safety or accuracy of evaluation results will also be excluded (29).

In addition, we will use structural MRI to calculate lesion volumes, including hemorrhage size (for hemorrhagic strokes) and infarct volume (for ischemic strokes). Automated or semi-automated segmentation tools (e.g., MRIcron, ITK-SNAP) will be applied to ensure accuracy and reproducibility (30). Lesion locations will be mapped to standardized brain atlases [e.g., Montreal Neurological Institute (MNI) space] using voxel-based or region-of-interest approaches. This will allow precise documentation of cortical/subcortical involvement (e.g., motor cortex, corticospinal tract, parietal regions) (31). Participants will be stratified into subgroups based on stroke type, lesion volume and location. What’s more, we will meticulously record the time elapsed from stroke onset to the initiation of rehabilitation, including the start of conventional rehabilitation therapy and AOT.

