### Randomization and blinding

2.5

Through a computerized block randomization protocol, the participants meeting the eligibility criteria will be randomly assigned to control group or experiment group. The random allocation sequence will be generated by the R package blockrand version 1.5, with randomly ordered blocks of size 6 or 8, and a 1:1 allocation ratio. The randomization cards generated by the blockrand version 1.5 package will be printed out and enclosed in sequentially numbered, opaque, sealed, and stapled envelopes. The allocation sequence will be concealed from the researcher responsible for enrolling and evaluating participants. Corresponding envelopes will be opened only after the enrolled participants have completed all the baseline assessments and at the time of allocation to the intervention. An independent study coordinator who will not oversee assessments and interventions will design and conduct the randomization sequence generation and group allocation. Only the study coordinator and principal investigator (PI) have access to group assignment materials locked in a binder.

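### Time since stroke onset is recorded but named neither in the allocation nor in the stated group comparison, which costs precision and carries any chance imbalance into the 4-week FMA-UE result

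*Protocol article*

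**What the plan says.** Section 2.4.1 sets the time window as "Within 6 months of stroke onset", with no numeric lower limit. Three other criteria in the same list restrict very early entry or narrow severity: "The disease is stable, neurological conditions and vital signs are no longer progressing", "The ability to sit independently for approximately 40 min" and "Brunstrom Recovery Stages for Upper Extremity 3, 4, or 5 stage at the time of enrollment".

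Section 2.5 describes the allocation sequence as produced by the R package blockrand "with randomly ordered blocks of size 6 or 8, and a 1:1 allocation ratio". It names no stratification factor.

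The closing paragraph of section 2.4.2 says "Participants will be stratified into subgroups based on stroke type, lesion volume and location". Time since onset is not in that list, and the sentence does not say whether it concerns allocation or analysis. The same paragraph promises to "record the time elapsed from stroke onset to the initiation of rehabilitation", and section 2.7 lists disease duration among the baseline data.

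The primary outcome is FMA-UE with an MCID of 4.25 points (2.7.1), measured before and after 4 weeks of intervention (2.7). For group comparisons, section 2.12 names the independent-samples t-test or, if its conditions fail, non-parametric tests. It names no covariate.

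**The concern.** Outcomes are taken only at baseline and 4 weeks, so any change that would occur in those weeks without the experimental component is part of the primary measure. If that change differs between patients who enter soon after stroke and those who enter close to 6 months, time since onset is a prognostic factor. Two things then follow. Its contribution stays in the residual variance of an unadjusted test, which costs power. And if one arm happens to receive more early entrants, the estimate in this trial is shifted, and a two-sample test has no means of removing the shift.

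The article itself treats the variable as worth careful recording, and its limitations paragraph says that variability between patients may affect interpretation. Yet no stated step of allocation or comparison uses it.

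**Working it through.** **1. The plan's own sample size.** Inputs from 2.10: d = 0.8, α = 0.05, power 0.85, independent-samples t-test. The noncentral-t calculation, two-sided, gives n = 29.05, hence 30 per arm (power at 30 per arm: 0.861). With 5% dropout, 30 / 0.95 = 31.6, hence 32 per arm. The stated figures reproduce. The calculation is in units of d and gives no SD or difference in FMA-UE points.

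**2. Size of a chance imbalance.** Assumption: patients fall into an early and a late class, with share f = 0.5 early. The article gives no distribution. An even split gives the largest imbalance.

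SD of the between-arm difference in early share = √(2f(1 − f)/n).
- n = 30: √(0.5/30) = 0.129. With fixed totals (hypergeometric), multiply by √(60/59) to get 0.130. The 95% limit is 1.96 × 0.130 = 0.255.
- n = 32: √(0.5/32) = 0.125, and the 95% limit is about 0.25.

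The hypergeometric probability of an imbalance of at least 25 percentage points is 0.07 (30 per arm) or 0.08 (32 per arm).

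**3. Shift in the FMA-UE difference.** Let D be the early-minus-late gap in 4-week FMA-UE gain that arises without any treatment effect. D is an assumption, so a range is shown. Shift = imbalance × D. At 30 per arm and f = 0.5:

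| D (points) | SD of shift | 95% limit | share of 4.25 |
|---|---|---|---|
| 2 | 0.26 | 0.51 | 12% |
| 4 | 0.52 | 1.02 | 24% |
| 6 | 0.78 | 1.53 | 36% |
| 8 | 1.04 | 2.04 | 48% |

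With a 30% or 70% early share the limits fall slightly (0.94 for D = 4, 1.87 for D = 8).

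A shift of half the MCID (2.125 points) at the 95% limit needs D ≈ 2.125 / (1.96 × 0.129) = 8.4, about twice the MCID.

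**4. Does it bias the test?** Ten thousand simulated trials were run with 32 per arm, balanced allocation, no treatment effect and an assumed within-class SD of 5. The mean difference was about 0 and the type I error 0.051 to 0.053 for D = 2 to 8. A shift of at least 2.125 points occurred in 0% of trials for D = 2 or 4, 0.4% for D = 6 and 3.0% for D = 8.

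**5. Given an imbalance that has occurred.** Under the same assumptions, with 20 early patients in one arm and 12 in the other (a 25-point imbalance), the unadjusted t-test rejects a true null in about 10% of such trials for D = 4 and 18% for D = 8. With 18 against 14 the rate stays near or below 5%. These conditional rates average out to about 5% over all allocations.

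**6. Precision.** The share of outcome variance explained by the split is R² = D² × 0.25 / SD². For an assumed total SD of 8 points:
- D = 4: R² = 16 × 0.25 / 64 = 0.06. Adjusting raises power from 0.861 to 0.882.
- D = 8: R² = 64 × 0.25 / 64 = 0.25. Adjusting raises power from 0.861 to 0.940.

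**The case against.** Unstratified blocked randomization with an unadjusted test is a valid design. Variation due to time since onset is already in the t-test's standard error, and α covers differences that arise by chance. That stands: steps 4 and 5 show no bias over repeated allocations. The cost is precision, and accuracy conditional on the imbalance that this trial happens to have.

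The documents also give no recovery rate, no FMA-UE SD and no expected distribution of onset times. That stands too, so every figure in points is conditional on D.

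A reader might infer that patients enter from the moment of stroke onset. The stability, sitting and Brunnstrom criteria do not support that; they keep out the earliest patients, although no numeric minimum is set.

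A reader might also infer that chance imbalance could readily move the result by half the MCID. That needs a gap of about 8 points, an even split and an imbalance at about the 95% limit, all at once. For a gap of 4 the limit is about a quarter of the MCID.

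Finally, this is a condensed article, and 2.12 mentions a statistical analysis plan that is not shown. Covariates may be specified there, and section 2.5 does not say outright that the list is unstratified. So it cannot be claimed that time since onset is used nowhere in the trial. But the article does state both its allocation method and its test, and the test as stated is unadjusted. The point concerns that stated method, not a detail left out.

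**Conclusion.** The point holds as one of efficiency and conditional accuracy. As stated, neither the allocation nor the group comparison uses a baseline value that the trial already collects and that may well be prognostic for a 4-week change score. With an even early/late split and 30 per arm, the 95% limit of the chance shift is about 0.5 points for a gap of 2, 1.0 for a gap of 4 and 2.0 for a gap of 8, against an MCID of 4.25. The gap, the split and the SDs are assumptions. If 4-week change does not depend on time since onset, nothing is lost. The stated test remains valid overall, so this is a worthwhile, low-cost improvement and not a flaw that undermines the trial.

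**What to change.** In 2.12, make the primary comparison a prespecified ANCOVA of 4-week FMA-UE on group, with baseline FMA-UE and time since onset at enrolment as covariates. State the form in which time since onset enters (continuous or in fixed classes) before unblinding. In 2.4.2, say whether the sentence on stratifying participants applies to the allocation list in 2.5 or only to subgroup analysis.

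The cost is one or two degrees of freedom and a model-based analysis in place of a two-sample test. No new data are needed, since baseline FMA-UE and time since onset are already collected.

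Stratifying the blockrand list by time since onset is optional, and only if recruitment has not begun. If it is done, keep the block sizes of 6 and 8. Smaller blocks would make upcoming allocations easier to guess in a single-centre trial whose participants and therapists are not blinded. If recruitment has begun, leave the list unchanged and rely on the covariate adjustment.
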